#### Qualitative studies

Some subjects will also be asked to participate in a qualitative study linked to the occupational rehabilitation intervention. The primary purpose of the qualitative studies is to reveal the participants’ and providers’ perception and experience with implementation of the rehabilitation programs. The study will further focus on the participants’ expectations before taking part in a multicomponent rehabilitation program and their experiences afterwards. In addition, the service providers’ rationale and experiences with the rehabilitation programs will be explored and compared to the participants’ experiences. The study will also explore facilitators and barriers to the RTW process as perceived by the different stakeholders (participants and providers). Data will be analysed according to the method of grounded theory
[42].

### Data collection

Data on sickness benefits and other social benefits will be based on register data from Statistics Norway as long as 5 years after participation in one of the rehabilitation programs. Self-reported data will be collected by electronic questionnaires via the internet (http://www.checkware.com) before pre-screening, at pre-test, post-test, and 3, 6 and 12 months after pre-test. Qualitative data will be collected through semi-structured focus group interviews, through individual interviews, and participant observations. Interviews will be based on an interview guide, audio recorded and transcribed. Some participants will keep notebooks during and after the rehabilitation program to explore their experience of the RTW process.

### Sample size

Three approaches have been performed to determine sample size:

1) Comparison of number of days with sick leave at 6 months of follow-up (P = 0.05; 90% power): An average of 60 days (SD 40) and 90 days (SD 60) of sick leave in the intervention and comparative group, respectively would require 61 persons for each group.

2) Comparison of time to sustainable RTW with Kaplan Meier survival analysis with log rank test with a hazard ratio of 0.6 (alpha 0.05, beta 0.20) would require 63 in each group (secondary outcome).Comparison of the share of workers after one year with the same statistical assumptions as point 1; 60% versus 40% RTW would require 68 people in each group. (secondary outcome).

Accordingly, with estimated ~20% loss to follow-up we will include 80 persons in each arm.

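### The log-rank figure of 63 per group counts events, not persons, so the stated 80% power for time to sustainable return to work does not hold at the plan's own one-year rates

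*Protocol article*

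**What the plan says.** The Sample size section of the Protocol article gives three calculations. The first, for the primary outcome (sick-leave days over 6 months), requires 61 per group at 90% power. The second concerns time to sustainable RTW and is marked as secondary: a "log rank test with a hazard ratio of 0.6 (alpha 0.05, beta 0.20) would require 63 in each group". The third, also secondary, is introduced as "Comparison of the share of workers after one year" and states that "60% versus 40% RTW would require 68 people in each group".

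The section then concludes that "with estimated ~20% loss to follow-up we will include 80 persons in each arm". No event probability, censoring pattern or follow-up time accompanies the log-rank figure. Under Secondary outcomes, the event is defined as full RTW held for at least four weeks without relapse. Under Data collection, register follow-up extends to as long as five years. No horizon is tied to the log-rank comparison.

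**The concern.** The power of a log-rank test depends on the number of events, not on the number of people enrolled. A sample-size statement therefore needs two steps: the events required, then the persons needed to produce them. The article appears to stop after the first step and use the result as a head count. It inflates for drop-out (63/0.8 = 78.75, consistent with 80) but makes no allowance for participants who have not returned to work when follow-up ends. The neighbouring calculation expects about half of them to be in that position at one year.

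What is at stake is how the secondary result is read. A non-significant log-rank comparison would be judged against a stated 80% power, and at one year the design does not have that power under any of the scenarios worked through here.

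**Working it through.** **Inputs, all from Sample size:** HR 0.6; "alpha 0.05, beta 0.20"; 63 per group; 60% versus 40% RTW at one year (mean 50%); 80 enrolled per arm; about 20% loss, leaving 80 × 0.8 = 64. Equal allocation is assumed. Sidedness is not stated. Two-sided is used because the primary figure reproduces that way: (1.960 + 1.282)² × (40² + 60²)/30² = 60.7, rounded up to 61.

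**Step 1: reproduce the stated 63.**
- Freedman: D = (1.960 + 0.842)² × [(1 + 0.6)/(1 − 0.6)]² = 7.85 × 16 = 125.6, rounded up to 126 events, or 63 per group. This is an exact match.
- Schoenfeld: D = 4 × (2.802)²/(ln 0.6)² = 120.3, rounded up to 121 events, or 60.5 per group.

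The printed 63 is the Freedman number of events per group.

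**Step 2: power with realistic event counts.** Total events D = 2 × (persons per arm) × (mean event probability).
- Schoenfeld power = Φ(√D × |ln HR|/2 − 1.960).
- Freedman power = Φ(√D × (1 − HR)/(1 + HR) − 1.960).

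For D = 80 and HR 0.6, Schoenfeld gives Φ(8.944 × 0.2554 − 1.960) = Φ(0.32) = 0.627, and Freedman gives Φ(8.944 × 0.25 − 1.960) = Φ(0.28) = 0.609.

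| Persons per arm followed | Mean event probability | Events | HR | Schoenfeld | Freedman |
|---|---|---|---|---|---|
| 63 | 50% | 63 | 0.6 | 52.7% | 51.0% |
| 64 | 50% | 64 | 0.6 | 53.3% | 51.6% |
| 80 | 50% | 80 | 0.6 | 62.7% | 60.9% |
| 80 | 40% | 64 | 0.6 | 53.3% | 51.6% |
| 80 | 60% | 96 | 0.6 | 70.6% | 68.8% |
| 63 | 50% | 63 | 0.557 | 64.0% | 61.6% |
| 80 | 50% | 80 | 0.557 | 74.3% | 71.9% |

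The last two rows take 60% versus 40% literally. Under proportional hazards these rates imply HR = ln(1 − 0.4)/ln(1 − 0.6) = 0.511/0.916 = 0.557, not 0.6.

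**Step 3: check by simulation.** Log-rank tests were simulated with exponential times, censoring at one year and 10,000 runs. With 40% RTW in the comparison arm and HR 0.6, power was 51% (63 per arm) and 61% (80 per arm). With 40% versus 60%, it was 63% and 74%.

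**Step 4: when the claim of 80% power would hold.**
- With 80 followed per arm: 120.3/160 = 75% (Schoenfeld) to 126/160 = 79% (Freedman) of participants must have the event.
- With the calculation's own 63 per arm: 126/126, so essentially everyone must have it under Freedman.

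**Step 5: detectable HR at 80% power with 80 events.**
- Schoenfeld: exp(−2 × 2.802/√80) = 0.53.
- Freedman: (1 − 0.313)/(1 + 0.313) = 0.52, where 0.313 = 2.802/√80.

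**The case against.** A reader might infer that the trial simply has 53-63% power for this outcome, or that 80 per arm is too few. The documents do not support either, for these reasons:

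- **The horizon is open.** No follow-up time is set for the log-rank test and registers run up to five years. If 75-79% eventually reach sustained RTW, 80 followed per arm does give 80% power. The shortfall is established at one year, not for every possible analysis time.
- **The rates belong to another endpoint.** The 60% and 40% are shares of workers at one year. The log-rank event is cumulative: someone who returned for four weeks and later relapsed has had the event but may be missing from the one-year share. The two can differ, which is why 40-60% overall is shown as a range.
- **HR 0.6 with 50% events is only one scenario.** Taken at face value, the plan's two rates imply HR 0.557 and 74% power with 80 per arm.
- **Loss may be small.** The outcome comes from registers, which the Strengths section says also cover non-responders. For this endpoint 80 per arm is arguably more relevant than 64, although the plan itself budgets about 20% loss.
- **The outcome is secondary.** The primary calculation reproduces, and 61/0.8 = 76.25 supports 80 per arm by itself.

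All of this stands, and it limits the size and importance of the point. It does not rescue the printed figure. A one-sided test would need 99 (Freedman) or 95 (Schoenfeld) events, so 63 persons per group would suffice with 75-79% events, but the article states neither condition and its primary calculation is two-sided. Nor is this detail properly left to an analysis plan: the article prints a number and uses it as persons.

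**Conclusion.** The point holds in a limited form. The figure of 63 per group is the two-sided Freedman event requirement for HR 0.6 at 80% power, presented as a head count. That conflicts with the one-year RTW rates in the same section.

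At one year, with all 80 per arm followed, power is roughly 61-63% for HR 0.6 if half have the event (53-71% by Schoenfeld for 40-60% overall), or about 74% under the implied HR of 0.557. With 63-64 evaluable per arm it is about 51-53%, or 64% under HR 0.557. None of these reaches 80%.

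The sizes assume a two-sided 5% test, proportional hazards, a one-year horizon, and the one-year share of workers as a stand-in for cumulative sustained RTW. This is a reporting error in a secondary-outcome calculation that should be corrected. It does not threaten the primary comparison or the enrolment target.

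**What to change.** Restate the second calculation as 126 events in total (63 per group) for HR 0.6, two-sided alpha 0.05 and 80% power. Add the assumed probability of sustained RTW and the follow-up horizon to which it applies, then give the resulting power or detectable HR for 80 per arm.

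Use one formula throughout. At 50% events and 80 followed per arm, Freedman gives 126 events required, 61% power at HR 0.6 and a detectable HR of about 0.52. Schoenfeld gives 121 events required, 63% power and a detectable HR of about 0.53. If the 60% and 40% rates are used to justify the event probability, say that they imply HR 0.557 and reconcile this with 0.6.

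The cost is one or two sentences and a less favourable stated power. No additional participants are needed, the primary calculation stays as it is, and an event-driven register cut is not needed to correct the error.

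### The 68 per group for one-year return to work (60% v 40%) is about half what the stated assumptions require, and 80 per arm less 20% loss does not reach even 68

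*Protocol article*

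**What the plan says.** The Sample size section of the protocol article gives three calculations.

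- **Primary outcome**, sick leave days over 6 months, with "P = 0.05; 90% power": "An average of 60 days (SD 40) and 90 days (SD 60) of sick leave in the intervention and comparative group" are assumed, and this "would require 61 persons for each group".
- **Time to sustainable return to work** (secondary), log-rank test, hazard ratio 0.6, alpha 0.05, beta 0.20: 63 per group.
- **Share at work after one year** (secondary), under the "same statistical assumptions as point 1; 60% versus 40% RTW would require 68 people in each group".

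The section closes: "Accordingly, with estimated ~20% loss to follow-up we will include 80 persons in each arm".

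**The concern.** The third calculation takes its alpha and power from the first, so all its inputs are fixed apart from sidedness. A 20-point difference centred on 50% is where the binomial variance is largest, and 68 per group looks far too small for 90% power. Separately, the closing sentence presents 80 per arm as following from the calculations above it, yet the largest of the three figures does not survive the stated loss.

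At stake is a published power claim. A reader who trusts it could take a non-significant one-year result as good evidence against a 20-point difference, when the trial would miss such a difference more than a quarter of the time at best.

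**Working it through.** **Inputs**, all from the Sample size section: proportions 0.60 and 0.40; equal groups; alpha 0.05; power 90%; loss about 20%; 80 enrolled per arm. Sidedness is not stated, so I first settle it on the neighbouring figures.

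**Reproducing the plan's other figures**

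- Point 1: n = (z₁₋α/₂ + z₁₋β)² (SD₁² + SD₂²)/Δ² = (1.960 + 1.2816)² × (40² + 60²)/30² = 60.7, so 61. This matches. One-sided would give 49.5, so 50.
- Point 2: events = (1.960 + 0.8416)² × [(1 + 0.6)/(1 − 0.6)]² = 125.6 (Freedman), so 126, or 63 per group. This matches.

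Both figures reproduce with two-sided 0.05, so two-sided is the natural reading of the third.

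**One-year share at work, two-sided 0.05, 90% power**

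- Unpooled: (1.960 + 1.2816)² × (0.24 + 0.24)/0.20² = 126.1, so 127 per group.
- Pooled: (1.960 × √0.50 + 1.2816 × √0.48)²/0.20² = 129.3, so 130 per group.
- Continuity-corrected: 140 per group.

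**Other readings at alpha 0.05** (n per group)

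| Sides | Power | Unpooled | Pooled | Continuity-corrected |
|---|---|---|---|---|
| Two | 90% | 127 | 130 | 140 |
| One | 90% | 103 | 106 | 115 |
| Two | 80% | 95 | 97 | 107 |
| One | 80% | 75 | 77 | 86 |

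None gives 68. Reading the reference to point 1 as a slip for point 2 (80% power) does not help.

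**Loss to follow-up**

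- 61/0.8 = 76.3, so 77: within 80.
- 63/0.8 = 78.8, so 79: within 80.
- 68/0.8 = 85: not within 80. Conversely, 80 × 0.8 = 64 < 68.
- 127/0.8 and 130/0.8 round up to 159 and 163 per arm.

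**Power actually available for 60% v 40%, two-sided 0.05**

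Pooled: Φ[(0.20√n − 1.960√0.50)/√0.48]. Unpooled: Φ[0.20√(n/0.48) − 1.960].

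| n per group | Pooled | Unpooled |
|---|---|---|
| 64 (80 less 20%) | 62% | 64% |
| 68 (as stated) | 65% | 66% |
| 80 (no loss) | 72% | 73% |

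**Detectable difference at 90% power**, centred on 50%: 28 points needs 65 per group and 25 points needs 82. So 64 per group detects about 28 points and 80 per group about 25 points, against the 20 stated.

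**The case against.** The arithmetic itself has no good defence. The objections concern its weight and the remedy.

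- **It is a secondary outcome.** This stands. The primary calculation reproduces and is covered by 80 per arm, so neither the recruitment target nor the primary comparison is in question. But the article gives a power for this outcome and lists it among the bases for the sample size, and that statement is wrong by a wide margin.
- **Register follow-up may leave little loss.** This stands in part. The Strengths section says the register supplies data from non-responders, and the Outcomes section draws the proportion at work from registers as well as self-report. If all 80 are analysable, the 64 v 68 shortfall disappears, as it does if loss is 15% or less (68/80 = 0.85). Power is then still only 72–73%. The article itself applies 20% loss without exempting this outcome, so its closing sentence fails on its own terms.
- **The wrong element may be an input and not the 68.** This is possible. At 90% power, 68 per group corresponds to a difference of about 27 points. The document does not show which figure was misstated, but as printed they cannot all be right.
- **Nothing in the article says the sample size rests on point 1 alone**, and 79 from point 2 is nearer to 80 than 77 from point 1. This carries little weight. The 63 per group is half of 126 events, and equals a number of patients only if everyone returns to work. That does not sit with 40–60% returning by one year.
- **Over-interpretation of a null result is a prediction.** That is fair. The misstated power is a fact of the text whatever readers later make of it.

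**Conclusion.** The concern holds on both counts. The stated 68 per group should be 127–130 (140 with continuity correction) at two-sided 0.05 and 90% power, so it is roughly half of what is required. The closing step to 80 per arm also contradicts the section's own figure, since 68 would need 85. The design has about 62–64% power for 60% v 40% after 20% loss and 72–73% with none, at least 17 points short of the 90% claimed.

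This rests on a normal-approximation comparison of two proportions with equal groups. The two-sided reading is inferred from the reproduced 61 and 63. The conclusion does not depend on it, because every one-sided variant at alpha 0.05 also exceeds 68. The error is confined to a secondary outcome and to the closing sentence.

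**What to change.** Replace the sentence on the share at work with wording such as: *A comparison of 60% v 40% at work after one year requires 130 per group for 90% power (97 for 80%), two-sided alpha 0.05. The planned 80 per arm gives about 72% power, or about 62% if 20% are lost, and the trial is not sized for this outcome.*

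Reword the closing sentence so that it no longer presents 80 per arm as satisfying all three calculations, and state that the sample size rests on the primary outcome (61 per group, 77 with 20% loss). If the original working shows that the proportions or the power were misprinted and 68 was intended, correct those inputs instead. Even then, 80 per arm with 20% loss would not retain 68, and the text must say so.

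The cost is a text change and a less favourable power figure for one secondary outcome. Enrolment need not change. Powering this outcome at 90% would take 163 per arm after 20% loss, about twice the plan.

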### Randomization

Sick-listed persons will be randomized twice (see Figure 
1). Firstly, subjects sick listed in the Social Security System will randomly receive one of two invitations (Long or Short program study) to participate in the study. Those allocated to not receive an invitation will serve as an unaware control group, and their future sick leave monitored. Secondly, invited subjects who provide informed consent and are found eligible, will be randomized to the control arm (single-component ACT-program) or to the already allocated Long or Short multicomponent rehabilitation program (depending on the outcome of randomization 1). Hence there are two separate randomized controlled studies at this level (Long vs. ACT and Short vs. ACT). Both randomizations are blinded. The first randomization will be performed by a project co-worker; and the second randomization by the Unit of Applied Clinical Research (third-party) at the Norwegian University of Science and Technology (NTNU). With anonymous aggregated data, we can also compare the reference group with those who 1) do not reply to the invitation, 2) decline participation and 3) are excluded after the pre-examination.

### Ethical considerations

REC Central - the Regional Committee for Medical and Health Research Ethics in Central Norway has approved these studies (No.: 2012/1241), and the trial is registered in clinicaltrials.gov (No.: NCT01926574). All participants enrolled in the study will take part in one of three rehabilitation programs in the specialist health care at St. Olav’s University Hospital. Those randomized to not being invited receive usual care, and the researchers will only be given anonymous aggregated information on outcome, sick-leave and sustainable RTW.

### Statistical analyses

Effect analyses of primary and secondary outcomes will be performed according to the intention to treat principle, and per protocol. For the primary outcome, difference in days of sick leave will be evaluated with the Mann Whitney U-test, as sick leave days are unlikely to be normally distributed. Sustainable RTW will be evaluated with survival analysis. Kaplan-Meier analysis will be used to describe association between groups and the duration of absence from work until sustainable RTW. Mixed models will be used to analyze time-dependent health outcomes and to estimate between group differences over time.

## Discussion

Sick leave is a major problem in the western world. Norway is considered to have a high level of sick leave
[43], and approximately 10% of the workforce is on disability pension
[44]. Hence, it is necessary to develop services that help people to stay at work, including effective rehabilitation models.

### Strengths

This trial will be the first to investigate whether a group based rehabilitation program for patients with musculoskeletal, mental or unspecific problems can facilitate work participation, whereas comparable studies have employed rehabilitation programs tailored for populations with a specific disorder (e.g. low back pain). Employing a national register for sickness absence data eliminates recall bias and provides data from non-responders. Furthermore, our design with randomization at two levels will make it possible to assess the effects of all interventions, and also determine the effect of contacting potential participants. Sending an invitation letter instead of recruiting from e.g. general practitioners will ensure that the group is not biased by referral, improving generalizability of the results. Moreover, the RCT will be followed by economic evaluations. Finally, the qualitative studies aim to explore the implementation of the rehabilitation programs more in depth. They will shed light on barriers and facilitators for implementation of such programs by studying the participants’ and providers’ perceptions before taking part in the intervention. A realistic evaluation approach would help to describe what providers and participants perceive as the important, helpful, or difficult aspects of an inpatient multicomponent rehabilitation program.

### Limitations

There are some limitations with this study. As in all interventions of this nature, blinding of participants or care providers is not possible. However, regardless of randomization outcome, all participants are given high quality rehabilitation by health professionals at St. Olav’s University Hospital. As in other countries, Norway has its distinct socio-economic and socio-cultural context. Therefore, the results cannot necessarily be generalized to other contexts. This occupational rehabilitation program is specifically tailored the Norwegian sickness benefit-, work-, health-, political systems and culture. Hence, implementation of these programs in other settings should be preceded by necessary modifications of the program.

### Impact of results

The knowledge to be generated will be important for both policy makers and clinicians and other professionals in practice. Decision makers will be given the best possible information, concerning the effect of this type of rehabilitation program. Furthermore, they will guide existing and new occupational rehabilitation programs. The main results of these studies will be published in 2015/16.
